**Ethical Considerations and project feasibility**

The study is reported and approved by the Danish Data Protection Agency, case number 1-16-02-152-22 and the Medical Research Ethics Committee, case number 2202151.

The study will be conducted according to Helsinki declaration. Participation in the study is voluntary. The participants will receive oral and written information and be guaranteed confidentiality. Written consent will be received from all patients. The study is registered on clinicaltrials.gov with the identification number NCT05270109.

The collaborating departments have the necessary professional competence, capacity and equipment, and each site has a co-investigator. All ENT departments have signed cooperation agreements, reference number 1-10-81-95-21 and data processor agreements, case number of the main agreement 1-52-81-216-21.

**Safety:** It is not expected that the intervention under investigation will cause risks or side effects other than the well-known related to tonsil surgery. All unexpected peri- and postoperative complications and adverse events will be registered. Furthermore, an interim analysis will be conducted after inclusion of 650 patients. Should the results of the interim analysis reveal that one of the interventions is associated with significant adverse events, the study will be terminated.

**Data sharing:** The data resulting from this study will be available from the corresponding author upon reasonable request.

**Discussion**

This protocol describes a Danish randomized controlled multicenter trial with the primary aim to evaluate whether IDTS tonsillectomy is non-inferior compared to cold steel tonsillectomy with regards to PTH and pain.

The study has four key strengths. The study is a randomized controlled trial with block randomization securing that patients are consecutively enrolled in the surgical treatment groups, a vital step to avoid selection bias. A further key strength is the multicenter setup considered the ideal way to generate data ready for generalization and enabling the enrollment of the large number of participants required for the protocol. In this study the multicenter setup entails cooperation of three regions including five treatment centers, hereunder as well secondary and tertiary treatment centers. The setup ensures a wide population-based inclusion in the project. Furthermore, the project will be both assessor blinded and blinded for the patients to prevent observer and confirmation bias.

There are also limitations to this study. The most significant limitation of the study is the lack of definition of PTH worldwide. The literature thoroughly describes primary and secondary bleeding occurring before and after 24 hours, respectively, but without a clear definition of severity. In this study we will define severity by interventions needed for PTH to accommodate this.

A potential limitation for the study is also one of the strengths - the multicenter setup inhabits a risk of one center not enrolling to equal measure of other centers, thereby entailing a selection bias. To remedy the selection bias of the center the dataset will potentially have to be excluded, which will weaken the results. The comprehensive logistics of multicenter studies sometimes result in unexpected heterogeneity in clinical practices between centers, which may induce confounders affecting the interpretation of the results.

In our study we have daily patient reported outcomes on pain management, which potentially will alter the patients’ compliance, also called the Hawthorne effect.

To our knowledge, the present study is the largest randomized controlled trial in ENT surgery in the Nordic countries to test the hypothesis whether IDTS tonsillectomy is non-inferior to cold steel tonsillectomy with regards to PTH, surgery time and postoperative pain.

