**Method**

*Design*

The project is designed as a Danish randomized controlled multi-center trial of tonsillectomy by conventional cold steel surgical technique versus IDTS. The study is blinded for patients until six months after surgery and the study is assessor blinded.

Randomization is computerized via the tonsil database and utilizes block randomization for each department in a random table of 2000 with equal numbers of group assignments. The randomization is only apparent to the surgeon on the day of the surgery and the day before.

*Course*

All elective and acute patients referred to tonsillectomy, with or without adenoidectomy, on benign indications will be assessed for eligibility at the participating ENT departments. Given a signed declaration of consent patients will be enrolled and randomized in the study to either the standard cold steel tonsillectomy or to IDTS tonsillectomy.

After surgery all patients will be brought to the recovery room for 1-4 hours or hospitalized for a day. Before hospital discharge a surgeon will check for postoperative hemorrhaging and the patient and caregivers will receive oral and written recommendations for the postoperative period. Patients or caregivers are requested to follow the recommendations, and they are instructed to contact the ENT department or to call an ambulance, if postoperative hemorrhage occurs.

There will be no planned postoperative visits at the hospital. During the first six postoperative months included patients/caregivers are asked to complete electronic questionnaires online on their mobile device: daily, for the first two postoperative weeks, and again one month and six months postoperatively.

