**Outcome Assessment**

Primary endpoints:

- Incidence of PTH defined as hemorrhage requiring hemostasis with bipolar electric coagulation, ligature, compression and/or medical treatment with anti-fibrinolytic within the first 24 hours after surgery (early PTH) until 30 days after surgery (late PTH).
- Intraoperative blood loss assessed by a standardized protocol utilizing the gravimetric method. The nurse suctions up 100 ml of NaCl weighed on the scale for precision (Kern & Sohn, PCB 6000-1). The suction canister is also weighed on the scale, as well as the dry gauze. After the surgery the canister of blood including the NaCl is weighed and the dry weights of the canister and gauze including the NaCl are subtracted, this leaves the total blood loss of the operation. It is assumed that 1 gram blood = 1 ml blood.
- Operative time in minutes from the Boyle-Davis gag is placed until it is removed. The operating nurse is responsible for measurements of time.
- Postoperative pain is assessed on an 11-point numeric rating scale ranging from 0 “no pain” to 10 “worst possible pain”. For children, the Wong-Baker Faces rating scale will be used.

Secondary endpoints:

- Patient reported: Unscheduled contacts to the health care system, patient satisfaction, health related quality of life, and patient reported quality of smell and taste via a validated TASTE questionnaire, followed by further investigation should the patient report altered taste at six months.

Variables:

- Patient reported outcome measures (PROMs) of postoperative recovery (return to normal diet, physical activity, and return to work, school, or childcare), compliance to postoperative recommendations.

**Inclusion criteria:** First time tonsillectomy due to; Tonsillar hypertrophy, recurrent tonsillitis (including previous peritonsillar abscess), chronic tonsillitis, systemic complications to tonsillitis, other (mononucleosis), PFAPA (periodic fever, aphthous stomatitis, pharyngitis, cervical adenitis), tonsillar plugs, peritonsillar abscess and signed written consent.

**Exclusion criteria:** Diseases in the hematopoietic system, antithrombotic or anticoagulant drugs in the recovery period, suspicion of or known malignancy, patients, or parents unable to read or speak Danish, patients, or parents unable to use online application for self-evaluation, patients or parents unable to give informed consent, body weight under 16 kilograms.

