**Power Considerations:** The sample size calculation is based on data from the Danish Tonsil Database. In a twelve months period, the frequency of PTH causing reoperation with hemostasis was 7.9%. With an expected non-inferiority treatment difference between the IDTS and the cold steel instrument, a significance level of 0.05, a power of 80%, and a non-inferiority limit of 4%, the required sample is 1126 patients. Assuming a drop out frequency of 10% into account, a total of 1250 patients are required. With a non-inferiority limit set to 4%, the present study will be able to detect a clinically relevant change in the frequency of PTH causing reoperation with hemostasis.

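### The PTH margin, event rate and sample size are set for reoperation, but the primary endpoint counts any treated bleed and reports no separate reoperation result

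*Protocol*

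**What the plan says.** Three parts of the protocol bear on this.

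- **Outcome Assessment, primary endpoints.** The event is "Incidence of PTH defined as hemorrhage requiring hemostasis with bipolar electric coagulation, ligature, compression and/or medical treatment with anti-fibrinolytic". The period is "within the first 24 hours after surgery (early PTH) until 30 days after surgery (late PTH"), so the only subdivision is by time. Neither the primary nor the secondary endpoints list a separate result for reoperation.
- **Power Considerations.** From a twelve-month period in the Danish Tonsil Database, "the frequency of PTH causing reoperation with hemostasis was 7.9" per cent. The calculation uses "a significance level of 0.05, a power of 80%, and a non-inferiority limit of 4" per cent, and arrives at 1126 patients, or 1250 after 10% dropout. It closes by saying that "the present study will be able to detect a clinically relevant change in the frequency of PTH causing reoperation with hemostasis".
- **Discussion, limitations.** The authors observe that the literature divides bleeds by time but does not define their severity clearly. Their answer is: "In this study we will define severity by interventions needed for PTH to accommodate this".

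**The concern.** The margin and the endpoint belong to different events. Followed as written, the trial compares the two arms on all treated bleeds and judges the difference against a limit chosen for reoperations. The power section nevertheless promises a conclusion about reoperation, and no listed endpoint supplies it.

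A single yes/no count gives a bleed managed with medication the same weight as one that returns the patient to theatre. If sealing changed the mix of bleeds as well as their number, the components could move in opposite directions and partly cancel. A non-inferior result on the pooled count would then be read, on the strength of the power section, as reassurance about reoperation that the data had not given.

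A larger sample would not cure this. It would restore power for the pooled count, but the components could still offset each other inside it.

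**Working it through.** **Inputs from the protocol.** Control rate 7.9% for reoperation; limit 4 points; alpha 0.05 (sidedness not stated); power 80%; 1:1 allocation (Design: "equal numbers of group assignments"); 1126 evaluable patients, so 563 per arm. A true difference of zero is assumed for sizing.

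**Step 1: reproduce the sample size.**

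n per arm = (z₁₋α + z₁₋β)² × 2p(1 − p) / Δ²

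= (1.6449 + 0.8416)² × 2 × 0.079 × 0.921 / 0.04²

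= 6.183 × 0.145518 / 0.0016 = 562.3, rounded up to 563, or 1126 in total.

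This matches exactly at one-sided 0.05. One-sided 0.025 gives 714 per arm, or 1428, which does not match. For dropout, 1126 / 0.9 = 1251, close to the stated 1250. So the sample size and the 4% limit rest on the reoperation rate.

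**Step 2: compare the events.**

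| Item | Event it refers to |
|---|---|
| 7.9% rate, 4% limit, 1126 patients, promised conclusion | Bleed leading to reoperation |
| Primary PTH endpoint | Bleed treated by any of four means, with no requirement for reoperation |

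The two would coincide only if every treated bleed led to reoperation. The endpoint's wording does not require that.

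**Step 3: how far could an offset mask a reoperation excess?** The protocol gives no rate for treated bleeds without reoperation ("minor" below), so every minor rate and every shift here is an assumption. Suppose reoperation is worse by the full limit, 7.9% v 11.9%. The probability of declaring non-inferiority, by normal approximation, is

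P = Φ[(0.04 − d)/SE − 1.645], with SE = √{[p_C(1 − p_C) + p_T(1 − p_T)]/563} and d = p_T − p_C.

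| Minor bleeds, control → IDTS | Rates compared | d | SE | P |
|---|---|---|---|---|
| Reoperation tested alone | 7.9% v 11.9% | 0.04 | 0.0178 | 5% |
| 6% → 6% (no offset) | 13.9% v 17.9% | 0.04 | 0.0218 | 5% |
| 2% → 1% | 9.9% v 12.9% | 0.03 | 0.0189 | 13% |
| 1% → 0% | 8.9% v 11.9% | 0.03 | 0.0182 | 14% |
| 6% → 4% | 13.9% v 15.9% | 0.02 | 0.0212 | 24% |
| 6% → 3% | 13.9% v 14.9% | 0.01 | 0.0209 | 42% |
| 6% → 2% | 13.9% v 13.9% | 0 | 0.0206 | 62% |
| 4% → 0% | 11.9% v 11.9% | 0 | 0.0193 | 67% |

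For example, with 1% → 0%: (0.04 − 0.03)/0.0182 − 1.645 ≈ −1.09, and Φ(−1.09) ≈ 0.14. At one-sided 0.025, the 6% → 2% row gives 49%, against 2.5% for reoperation alone.

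**Step 4: power of the possible decision rules, with no true difference and 563 per arm.**

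| Event judged against the 4% limit | Minor bleeds 2% | Minor bleeds 6% |
|---|---|---|
| Reoperation only | 80% | 80% |
| Pooled count only | 73% | 62% |
| Both required (by simulation) | 70% | 58% |

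**The case against.** The Discussion sentence on severity need not promise grades. It can mean that a bleed is severe enough to count once it needs one of the listed interventions, and the endpoint does exactly that. This objection stands. A reader might infer that the protocol committed itself to ordered severity grades and then dropped them, but the text does not prove it. Even on the threshold reading, severity among the counted bleeds stays unseparated, and the conflict between the endpoint and the power section is untouched.

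Grades or component tables may also exist elsewhere. The protocol mentions a table of measurements and definitions whose content is not shown, a SAP may exist, and the Figure 2 legend says the doctor enters a detailed account of each bleed. This too is fair, so the absence of a grading scale is not itself a fault here. A graded report elsewhere would still leave the primary endpoint, as the protocol fixes it, on a different event from its margin.

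Finally, the masking scenario is constructed. Nothing in the protocol suggests that reoperations would rise while minor bleeds fall. The high figures need a large opposing shift: 6% → 2% means minor bleeds fall by two thirds while reoperations rise by half. With small minor-bleed rates the pass probability rises only from 5% to about 13% or 14%. That limits what can be said about size, but not the mismatch itself.

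**Conclusion.** The point holds as an inconsistency between two sections of the protocol. The rate, limit, sample size and promised conclusion concern reoperation; the endpoint to be judged by them is any treated bleed. As written, the trial has no listed result that answers the reoperation question.

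Masking is possible, but its size is unknown. With reoperation worse by the full 4 points, the pooled test passes between 5% of the time (no offset) and 62% (minor bleeds 6% → 2%), or 67% in the extreme 4% → 0% case, against 5% for reoperation alone. These figures rest on assumed minor-bleed rates and shifts, 563 per arm and a one-sided 0.05 limit. A reader might take the upper figures as a forecast, or as a sign that IDTS raises reoperations. The documents support neither, since they give no minor-bleed rate and no evidence of opposing shifts.

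**What to change.** Reconcile the Outcome Assessment with the Power Considerations before unblinding.

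- **Preferred:** pre-specify PTH leading to reoperation, coded from the doctor's database account, as the event to which the 4% limit applies. This keeps the stated 80% power at 563 per arm. The pooled count is still reported.
- **Minimum:** keep the pooled endpoint, and report the reoperation risk difference with its confidence interval against the 4% limit beside it.

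In either case, draw the reoperation conclusion only from the reoperation result. One sentence in the Discussion should say whether defining severity by intervention means a threshold for counting or a classification.

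The cost is some protocol wording and one more pre-specified analysis on data that the account of each bleed should already hold. A pooled non-inferiority result could also no longer be read as covering reoperation. Requiring both results to pass is a further option, but a trade-off: joint power would be about 70% to 58% if minor bleeds add 2% to 6%. An ordered severity scale with its own model is a choice for the SAP and is not needed to settle this point.

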**Statistical analysis**

Endpoints will be evaluated as differences between treatment groups. Categorical data are analyzed by chi2 or Fisher’s exact test. Depending on normal distribution, continuous data is analyzed by either un-paired Student’s *t-test* or Mann-Whitney rank sum test. An Intention-to-treat principle will be used including all randomized participants in the analysis. Stratification will be performed, and confounding factors (sex, age, surgical indication, BMI, smoking, comorbidity) analyzed in a multiple logistic regression model. Repeated measurement data will be analyzed in a mixed effect model for repeated measurements (ANOVA) with group and time as systematic factors and patients as random effect. The model takes random variations over time into account. Post-hoc tests will be based on the Kenward-Roger approximation to test all included patients despite missing data. The significance level is set at 0.05.

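### The Discussion allows an under-enrolling center to be excluded, which contradicts the intention-to-treat rule and remedies no bias in the arm comparison

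*Protocol*

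**What the plan says.** Four places in the protocol bear on this.

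- **Discussion, limitations.** The multicenter setup is said to carry "a risk of one center not enrolling to equal measure of other centers, thereby entailing a selection bias". The remedy follows at once: "To remedy the selection bias of the center the dataset will potentially have to be excluded, which will weaken the results". The same paragraph also warns of "unexpected heterogeneity in clinical practices between centers, which may induce confounders affecting the interpretation of the results".
- **Statistical analysis, population.** "An Intention-to-treat principle will be used including all randomized participants in the analysis". No exception is stated.
- **Method, Design.** Randomization "utilizes block randomization for each department in a random table of 2000 with equal numbers of group assignments".
- **Statistical analysis, models.** One sentence opens with "Stratification will be performed", without naming a factor, and goes on to "confounding factors (sex, age, surgical indication, BMI, smoking, comorbidity) analyzed in a multiple logistic regression model". The repeated-measures model is described "with group and time as systematic factors and patients as random effect". Department is named in neither model.

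**The concern.** The exclusion sentence and the intention-to-treat sentence define different primary analysis sets, and nothing in the protocol says which prevails. Removing a center removes randomized patients.

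The reason given does not support the removal. Selection bias in the arm comparison would require the two arms to differ systematically in whom they contain. Blocked 1:1 allocation within each department prevents this at any center size. If the authors mean instead that the sample would not represent the population, dropping a center removes still more of that population.

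The exclusion is also unspecified: how low enrolment must be, who decides, when, and with what knowledge of the outcome data. In a non-inferiority trial judged against a 4-point margin on post-tonsillectomy hemorrhage (PTH), an analysis set that can be chosen late weakens the claimed 0.05 error rate.

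**Working it through.** **1. The protocol's sample size.** From Power Considerations: PTH rate 7.9% (taken as equal in both arms), margin 4 percentage points, significance level 0.05, power 80%, 1126 patients, raised to 1250 for 10% dropout.

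n per arm = (z₁₋α + z₁₋β)² × 2p(1−p) / margin²

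- One-sided 0.05: (1.645 + 0.842)² × 2 × 0.079 × 0.921 / 0.04² = 562.3, so 563 per arm and 1126 in total. This matches exactly.
- One-sided 0.025: 714 per arm and 1428 in total, which does not match. The stated 0.05 is therefore one-sided, and it is used below.
- Dropout: 1126 / 0.9 = 1251, close to the stated 1250.

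**2. Does unequal center size bias the comparison?** Let center k hold n_k of N patients, half in each arm, with true risk difference δ_k. The expected crude difference is Σ (n_k/N) δ_k. If δ_k is the same δ everywhere, the sum equals δ for any set of center sizes, with or without a given center. If the δ_k differ, dropping a center only changes which centers are averaged; it removes no imbalance between arms.

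A simulation agrees. The assumptions were center sizes 350, 325, 300, 225 and 50, PTH rates from 4% to 14% by center, 1:1 allocation within center and no true difference. The mean estimated risk difference was within 0.0003 of zero both with all centers and without the smallest, with a standard deviation of 0.014 in each case.

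**3. Power after an exclusion.** Power = Φ(0.04/SE − 1.645), with SE = √(2 × 0.079 × 0.921 / n per arm). The excluded share is an assumption. The Discussion counts five centers, so one that under-enrols relative to the others holds less than a fifth.

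| Share excluded | Evaluable | SE | Power |
|---|---|---|---|
| 0% | 1126 | 0.0161 | 80.0% |
| 2% | 1103 | 0.0162 | 79.3% |
| 5% | 1070 | 0.0165 | 78.2% |
| 10% | 1013 | 0.0169 | 76.3% |
| 20% (limit) | 901 | 0.0180 | 71.9% |

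**4. What an outcome-informed choice could do.** This is a worst case, not a forecast. Set the true difference at the margin (7.9% against 11.9%), with 563 per arm and a one-sided 5% test. With all centers, false non-inferiority is declared in about 5% of simulated trials. If the smallest center is dropped whenever that turns failure into success, the rate is about 6%, 6.5% and 7% for assumed shares of 5%, 10% and 20%.

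**5. What naming department would gain for PTH.** Assume five equal centers with rates of 4, 6, 8, 10 and 14%. The mean is 8.4%. The between-center variance is (4.4² + 2.4² + 0.4² + 1.6² + 5.6²)/5 = 11.84 squared percentage points, or 0.00118. Against 0.084 × 0.916 = 0.0769 this is about 1.5% of the variance, so the standard error changes by under 1%.

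**The case against.** The strongest defense is that the exclusion sentence sits in a limitations paragraph, is hedged, admits its own cost and sets no analysis rule; the Statistical analysis section governs. Its trigger is enrolment, which can be known without outcome data. These points have force. A reader might infer that the protocol plans to drop a center, or means to do so on results. The text supports neither: it allows an exclusion and ties it to enrolment. What the defense does not remove is the conflict itself, or the absence of a threshold, a time and a decision-maker, without which the choice is not protected from knowledge of results.

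It can also be said that selection bias here may mean representativeness, since the same section praises wide population-based inclusion. That reading is plausible, but exclusion would work against it.

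On size, the loss for a center that truly under-enrols is a few points of power. If nobody dropped out, 1250 less 10% leaves 1125 patients and 80% power, although that allowance is meant for dropout.

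A reader might further infer that department is ignored in the analysis and that the results would be biased or the standard errors invalid. The documents do not show this. The stratification clause names no factor, so department is not ruled out, and a statistical analysis plan not seen here may specify it. With 1:1 blocks within department, leaving it out makes standard errors slightly too large, which is conservative for non-inferiority.

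**Conclusion.** The point holds as a contradiction within the protocol. The Discussion permits a post-randomization exclusion that the intention-to-treat sentence forbids, for a reason that does not apply to the arm comparison under randomization within department. An unseen analysis plan would not reconcile the two sentences in this document.

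The power loss is secondary: about 2 to 4 points for an assumed share of 5% to 10%, and 8 points at the limit of an equal fifth. Quoting 72% as the expected result would overstate the case, because a center with an equal fifth is not under-enrolling. These figures rest on a 7.9% rate in both arms and a one-sided 5% test. The main consequence is an analysis set that could be settled after results are known. The rise in false non-inferiority to about 6% to 7% is an illustration that assumes an opportunistic decision, which the protocol does not describe.

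The absence of department from the listed model terms is an opportunity for a small gain in precision. It is not a source of bias.

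**What to change.** 1. Delete the exclusion sentence from the Discussion. If the paragraph keeps unequal enrolment as a limitation, describe it as a limit on generalization.
2. State in the Statistical analysis section that every randomized patient at every center belongs to the primary analysis, whatever the center's enrolment.
3. Present leave-one-center-out results as a pre-specified sensitivity analysis only. This also addresses the concern about differing practice between centers.
4. As a secondary improvement, name department as the factor in the stratified PTH analysis (for example a Mantel-Haenszel risk difference) and as a term in the logistic and mixed models. Very small centers may be pooled in the model, but not removed.

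The cost is a change of wording, one model term and one extra table. Sample size and trial conduct do not change.
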